### Study participants

Eligible cases will be Queensland residents, aged 45-64 years, with a histologically confirmed diagnosis (notified to the Queensland Cancer Registry (QCR)) of primary colorectal cancer between January 2010 and September 2011, and in paid employment at the time of their cancer diagnosis. The QCR has universal coverage of persons diagnosed with cancer residing in Queensland. Study exclusions include: cognitive impairment; not speaking English; having no telephone; and previous or concurrent cancers (except non-melanoma skin cancer). A general population comparison group will be randomly selected from a secondary data source, the Household, Income and Labour Dynamics in Australia (HILDA) Survey dataset, using retrospective data in Waves 9 and 10 (2009 and 2010 data). HILDA is an Australian household panel survey which began in 2001 and collects information about economic and subjective well-being (including HRQoL), labour market and family dynamics. Households and individuals are followed up annually through interviews and self-administered questionnaires. Each new survey wave of HILDA, is developed and pilot-tested over a 9-month period using a sample of urban and rural households prior to data collection.

Ethics approval for the study was obtained from the Human Ethics Research Committees of Queensland Institute of Medical Research, Griffith University and the Queensland Health Research Ethics and Governance Unit.

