### Sample size

Based on cancer incidence [16] and labour figures [17] it is anticipated that at least 522 working persons with colorectal cancer will be eligible annually. Sample size calculations were based on the number required to detect a 15% difference in work participation between workers with and without cancer assuming a 5% significance level and 80% power. Based on our past experience of recruiting colorectal cancer patients through the QCR and allowing for 85% doctors consent, 70% participant consent, 90% baseline interview completions and 75% retention at 12 months post-diagnosis, we will require initial contact with 258 patients with colorectal cancer to retain 125 patients at 12 months. The wave-on-wave attrition rates among continuing HILDA respondents have been consistently low, approximately 5% each year [18]. Data for 2,590 employed persons enrolled in HILDA aged 45-64 years Australia-wide will be available. HILDA data will be randomly matched 2:1 to patients with colorectal cancer, by gender and 5-year age category. Thus the total sample size to be selected for the study will be approximately 780.

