### Data collection sources

Data will be collected during this project from four sources (Table 1):

**Table 1 T1:** Questionnaire item domains at each time point by cancer cases and general-population comparison group

	Cancer Group		Comparison Group
**Method**	**Telephone interview**	**Mailed questionnaire**	**Face-to-face interview**

Time 1^a^	1. Socio-demographics^b^ 2. Cancer treatments 3. Symptoms (MSAS^b^) 4. Work questions^a^ 5. Work limitations (WLQ)	6. Quality of life (SF-36)^b^ 7. Health behaviours & conditions^b^ 8. Cancer-specific quality of life (FACT-C) 9. Financial strain^b^	Question groups 1, 4, 6, 7, 8, 9 from HILDA Wave 9, 2009 data

Time 2	Repeat question groups 2-8		Question groups 1, 4, 6, 7, 8 from HILDA Wave 10, 2010 data

^a ^Time 1 for the Cancer Group occurs six-months after diagnosis however retrospective work questions are asked about their time of diagnosis (baseline) and about their current time (six months after diagnosis) therefore a common one year period will be compared across the cancer and comparison groups for key work questions.

^b^These questions are the same as those in the comparison group to enable direct comparison between groups.

Abbrevs: FACT-C = Functional Assessment in Cancer Therapy plus Colorectal Cancer module, HILDA = Household, Income and Labour Dynamics in Australia, MSAS = Memorial Symptom Assessment Scale, SF-36 = Medical Outcomes Study Short Form 36, WLQ = Work Limitations Questionnaire.

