#### 2) Telephone interviews (cancer group)

Participants with cancer will take part in structured telephone interviews at 6 and 12 months after diagnosis. At the 6-month data collection time point we will also ask participants to recall work-related information at the time they were diagnosed with cancer (baseline). Telephone interviews will be undertaken in order to maximise response rates, reach a wide geographical region and minimise participant burden, the latter being important in a working population that may require out-of-hours contact. Interviews will be conducted by trained and experienced interviewers. To minimise respondent burden, interviews will be kept to approximately 30 minutes each. A flexible interview schedule will be adopted and tailored to suit the schedules of working participants.

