### Analyses

All analyses will include gender as a factor and will test for interactions of gender with other factors in the model. Gender differences are important, as not only do men and women have different work participation rates, work hours and occupation types in the general population [17], they respond and adjust differently to illnesses, have different health behaviours and other risk factors for cancer [24]. Where no effect modification is observed, pooled results will be presented. Socio-demographic characteristics will be compared at baseline to identify any statistically significant differences between the cancer and comparison groups. Descriptive analyses will be conducted to chart employment transitions over the year since diagnosis among the cancer group and over 2009-2010 year period among the comparison group. Although the first time point for the cancer group is six months after diagnosis, participants are asked to recall work circumstances (occupation type, hours worked, industry etc) at the time of diagnosis (retrospectively) and at time 1 (six months after diagnosis). Separate multivariable logistic regression modelling will identify explanatory variables that are significantly associated with work participation in the cancer and comparison groups. For these models, adjusted odds ratios with 95% confidence intervals and p-values will be computed. Cox proportional hazards models will assess time to work resumption in the participants with cancer and significant correlates of timely work re-entry. Mixed-effects modelling for the cancer group will be used to examine change in HRQoL scores (time 1 - time 2) by participants who reduce or leave in that time versus those who do not. We will also compare HRQoL scores between the cancer and comparison groups at time 2. Data on work limitations measured in the cancer group will be scored across the four domains and mixed-effects modelling undertaken to assess changes in scores between time 1 and time 2. Reasons for study withdrawal in the cancer sample will be closely monitored. Descriptive analyses of baseline variables for the 'completers' and 'non-completers' will identify any possible bias and the source and, if necessary, subsequent analyses will be weighted accordingly. In the comparison group, only responders at both HILDA Waves 9 and 10 will be included.

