## Discussion

Despite the considerable number of Australians of working ages being diagnosed with cancer each year, surprisingly little is known about the impact of cancer on the workforce. With an ageing population, the Australian Government has recently implemented policies to encourage people to remain working longer and has increased access to personal superannuation funds and social security benefits (e.g. pension bonus schemes). The challenges presented to 'baby boomers' (those born during 1946-1961) differ from those facing previous generations because, as they approach normal retirement age, they may face caring responsibilities for both elderly parents and young grandchildren [27]. Female baby boomers may be disadvantaged financially due to working in occupations that were traditionally low-paid and female-dominated (i.e., nursing, secretarial, retail, teaching) and before equal pay legislation (pre-1960s) and compulsory superannuation laws. They may also have taken longer periods off work to raise families, compared to subsequent generations, and so collectively may have little retirement savings and financial security [27]. Middle-aged men with cancer may be at the height of their careers, and their sense of self may be strongly attached to their work roles. Therefore, cancer may negatively affect a person's employment and financial situation and fuel the anxiety and distress created from facing a life-threatening illness.

Our research will extend the current literature and improve our understanding in this field. The translation of current knowledge into supportive care practice is limited because of the use of retrospective or cross-sectional designs and/or, patient groups from a single clinical setting, a dominance of breast cancer among the patient samples and, importantly, the inability to isolate the effects of ageing, retirement choice and labour force changes due to the lack of a non-cancer control group. Our study will overcome these limitations by recruiting a population-based sample and using validated instruments, including a non-cancer comparison group and utilising both a prospective and retrospective design. We have chosen colorectal cancer because this cancer type is the most common to both men and women, and we will have a homogenous disease group from which to compare men and women.

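### Comparators are observed from 2009 to 2010 and cases from 2010-11 to 2011-12, so the hypothesis 1 contrast mixes calendar period with cancer

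*Protocol article*

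**What the plan says.** - **Cases.** The Study participants section admits people diagnosed with "primary colorectal cancer between January 2010 and September 2011". The telephone interview section sets "structured telephone interviews at 6 and 12 months after diagnosis".
- **Comparators.** They are selected from HILDA "using retrospective data in Waves 9 and 10 (2009 and 2010 data"). The Abstract, Table 1 and the section on general-population survey data name the same two waves.
- **Analysis.** Employment transitions are charted "over the year since diagnosis among the cancer group and over 2009-2010 year period among the comparison group".
- **Alignment.** Table 1, footnote a explains that cases recall their work at diagnosis, and "therefore a common one year period will be compared across the cancer and comparison groups for key work questions".
- **Matching.** HILDA data are "randomly matched 2:1 to patients with colorectal cancer, by gender and 5-year age category" (Sample size). Neither the matching nor the Analyses section mentions calendar time.
- **Purpose.** The Discussion lists among the limits of earlier work "the inability to isolate the effects of ageing, retirement choice and labour force changes due to the lack of a non-cancer control group", and says that this study will overcome them. The Background likewise faults the earlier Australian colorectal cohort because it could not tell who would have left work without cancer.

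**The concern.** Hypothesis 1 contrasts the two groups: the proportion who stop work or change their hours by at least 20% within 12 months is expected to be more than 15% higher in cases than in the community. The comparison group supplies the background rate. If it supplies the rate for 2009 to 2010 while the cases live through 2010 to 2012, any difference in background job loss, hours cuts or retirement between those periods is counted as an effect of cancer. Labour force change is by nature tied to calendar time, and it is one of the three things the Discussion says the comparison group will isolate.

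The phrase about a common one-year period in footnote a could lead a reader to think that this has been handled.

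**Working it through.** No stated figure is in dispute; the point rests on dates.

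**1. Windows.** Case end date = diagnosis + 12 months.

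| | Start | End |
|---|---|---|
| Cases | Jan 2010 to Sep 2011 | Jan 2011 to Sep 2012 |
| Comparators | 2009 | 2010 |

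Every comparator baseline precedes the first diagnosis, and no 12-month case outcome falls in the comparators' outcome year.

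**2. Overlap.** The article does not give the HILDA interview month, so it is varied over the whole of 2010. Count months from the start of January 2010. Take diagnoses at t = 0.5, 1.5, ..., 20.5 (21 months, uniform accrual assumed). The case window is [t, t + 12]. With the 2010 interview at month s, the comparator window is [s - 12, s]. Since t is positive, overlap = max(0, s - t), and the case window starts t - (s - 12) months later. Mean t is 10.5, so the mean lag is 22.5 - s.

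| 2010 interview at s | Mean overlap, months (of 12) | Diagnosis months with no overlap | Mean lag of start, months |
|---|---|---|---|
| 0 (start of year) | 0.0 (0%) | 21 of 21 (100%) | 22.5 |
| 6 | 0.9 (7%) | 15 of 21 (71%) | 16.5 |
| 12 (end of year) | 3.4 (29%) | 9 of 21 (43%) | 10.5 |

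**3. How a period difference enters.** Let r0 be the background rate of stopping or cutting hours in the comparators' period, r1 the background rate in the cases' period, and c the added effect of cancer in percentage points. The estimated contrast is (r1 + c) - r0 = c + (r1 - r0). The second term is the bias, one-for-one. All comparators share one wave pair, so a calendar covariate fitted to these data has almost nothing with which to separate r1 - r0 from c.

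**4. Illustration only.** The article gives no labour-market rates. Assume r1 - r0 of 2 to 5 points: 2/15 = 13% and 5/15 = 33% of the 15-point planning difference. Take 125 cases retained at 12 months (Sample size), 2 x 125 = 250 comparators, a two-sided 5% z-test of two proportions with pooled null variance, and an assumed comparator rate of 10% to 25%:

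| Assumed shift | True cancer effect | Probability of a significant result |
|---|---|---|
| 0 | none | 5% |
| +2 points | none | 7-10% |
| +3 points | none | 10-15% |
| +5 points | none | 18-31% |
| 0 | 15 points | 84-95% |
| -5 points | 15 points | 53-75% |

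A shift can thus create an apparent effect or hide a real one.

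**5. After the fix.** If each case is set against the wave pair starting in its diagnosis year (2010 to 2011, or 2011 to 2012), the same calculation gives a mean overlap of 5.4 to 9.2 months of 12 (45% to 77%), depending on interview month. The required sample size does not change.

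**The case against.** The strongest reply is that the waves are openly stated throughout, that the group still does most of its job, and that nothing shows the two periods to differ. Much of this stands.

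- An age- and gender-matched one-year panel does capture age-related exit and ordinary retirement and turnover. Only the period-specific part is left in.
- No passage gives exit or hours-reduction rates for 2009 to 2012. The bias could be near zero or could run in either direction. The 13% to 33% above is the assumption divided by 15.
- The exposure is mainly Aim 1 and hypothesis 1, and potentially the time-2 quality-of-life comparison between groups. The Cox, work-limitation and quality-of-life change models use cases only, and the participation models are fitted separately by group.
- The windows can overlap in part within 2010 for early diagnoses.
- The article does not say when later waves are released. Release timing may explain the choice of waves, but no reason is given.

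Two stronger readings are tempting and should not be drawn. One is that the policies to keep people working, which the Discussion calls recent, changed conditions between the two windows. They are undated and may have been in force throughout both. The other is that no analysis could ever separate period from cancer. That holds for a regression on Waves 9 and 10 alone, but HILDA has run annually since 2001, and other wave pairs can address it.

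What the reply does not meet is the mismatch itself: nothing in the matching or the analysis corrects it, and footnote a does not disclose it as a difference in dates.

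**Conclusion.** The concern holds as a calendar mismatch that leaves hypothesis 1 open to period confounding of unknown size and direction. On the article's own dates, the case windows start on average 10.5 to 22.5 months after the comparators' windows and share 0% to 29% of the 12 months, assuming uniform accrual and an interview at any time in 2010. The planned data cannot separate a period shift from the effect of cancer. To that extent the Discussion's claim about labour force changes is not supported, while its claims about ageing and ordinary retirement are less affected. It would go too far to say that the study's contrast is biased: the documents show that it is exposed, not by how much. The point should be acted on because the remedy uses a panel already in the study.

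**What to change.** Match each case, on gender and 5-year age group as planned, to comparators from the wave pair that starts in the year of diagnosis: Waves 10-11 for 2010 and Waves 11-12 for 2011 (wave years inferred from the article's annual numbering).

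If those waves are not released in time:

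1. Report the Waves 9-10 comparison first, with the period difference stated as a limitation.
2. Repeat the primary contrast with the later waves once they are available.
3. Meanwhile, use earlier annual wave pairs to show how much exit and hours-reduction rates vary from year to year.

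If the Waves 9-10 comparison is used, reword footnote a to say that the two periods are equal in length only.

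Cost: the comparison may wait for a data release, although case follow-up itself runs to September 2012. Calendar alignment improves but is not complete (step 5 of the working).

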### Sample size

Based on cancer incidence [16] and labour figures [17] it is anticipated that at least 522 working persons with colorectal cancer will be eligible annually. Sample size calculations were based on the number required to detect a 15% difference in work participation between workers with and without cancer assuming a 5% significance level and 80% power. Based on our past experience of recruiting colorectal cancer patients through the QCR and allowing for 85% doctors consent, 70% participant consent, 90% baseline interview completions and 75% retention at 12 months post-diagnosis, we will require initial contact with 258 patients with colorectal cancer to retain 125 patients at 12 months. The wave-on-wave attrition rates among continuing HILDA respondents have been consistently low, approximately 5% each year [18]. Data for 2,590 employed persons enrolled in HILDA aged 45-64 years Australia-wide will be available. HILDA data will be randomly matched 2:1 to patients with colorectal cancer, by gender and 5-year age category. Thus the total sample size to be selected for the study will be approximately 780.

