### Recruitment

As mandated by QCR protocols, patients' names and the names of their doctors will be accessed via the QCR and initial letters sent to each patient's doctor requesting permission for the patient to be approached, followed by reminder letters and telephone calls if necessary. All patients for whom doctor's consent is obtained will be mailed a study invitation letter, an information sheet and consent form. Three weeks after the initial patient letter, non-responders will be telephoned to gauge their interest in the study and screened for their eligibility.

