#### 1) Pathology reports held within the QCR (cancer group)

Clinical data will be collected including tumour site, histopathological tumour type, degree of differentiation/grade, degree of metastasis and stage of disease (e.g, TNM or Dukes staging).

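### The 258 initial contacts do not give 125 retained cancer cases at the stated rates (about 312 are needed), and the chain does not say whether contacts are registry patients or eligible workers

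*Protocol article*

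**What the plan says.** All references are to the protocol article.

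- **Sample size, target.** The study is sized to "detect a 15% difference in work participation between workers with and without cancer", "assuming a 5% significance level and 80% power". The base rate and the sidedness of the test are not given.
- **Sample size, chain.** The contact number is reached by "allowing for 85% doctors consent, 70% participant consent, 90% baseline interview completions and 75% retention at 12 months post-diagnosis", and the result is that "we will require initial contact with 258 patients with colorectal cancer to retain 125 patients at 12 months". None of the four rates is for eligibility.
- **Sample size, pool.** It is anticipated that "at least 522 working persons with colorectal cancer will be eligible annually", a figure built from incidence and labour statistics.
- **Study participants.** Cases must be aged 45-64 "and in paid employment at the time of their cancer diagnosis". Cognitive impairment, not speaking English, having no telephone and other cancers are exclusions.
- **Recruitment.** Patients' and doctors' names come from the registry. Doctors are written to first, then every patient whose doctor agrees. Three weeks later "non-responders will be telephoned to gauge their interest in the study and screened for their eligibility".
- **Registry data.** Under the heading on pathology reports: "Clinical data will be collected including tumour site, histopathological tumour type", then grade, metastasis and stage. No work item is listed.
- **Abstract and Sample size, totals.** The Abstract describes 260 cases in paid employment and 520 comparators. Sample size gives a total of about 780 at 2:1 matching.

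**The concern.** Two things look wrong in the step from contacts to retained cases.

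First, the printed contact number does not follow from the printed rates. Second, the chain begins at contact, which as described comes before eligibility is checked, yet it treats every contact as someone who can count towards the 125. Any contact who was not in paid work at diagnosis, or who meets an exclusion, is lost without a rate to cover it.

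The 125 is the number behind the 80% power statement. If recruitment is planned on 258 contacts, the expected number of analysed cases is lower than the power statement assumes. The number 260, which appears to be 258 rounded, is also presented as the study's case sample and sets the 520 comparators and the total of 780. The same figure therefore serves both as letters sent and as cases enrolled.

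**Working it through.** **Inputs from Sample size:** rates 0.85, 0.70, 0.90 and 0.75; 258 contacts; 125 retained; 15-point difference; 5% level; 80% power; 2:1 matching; 522 eligible workers a year. **Input from Study participants:** a diagnosis window of January 2010 to September 2011, which is 21 months. **Assumed, because not given:** the eligible share w among contacts, the base rates, and a two-sided test.

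**1. Is 125 a sensible target?** The pooled-variance formula for two proportions (2:1, two-sided 5%, 80% power) gives 126 cases for 50% v 35%, 128 for 65% v 50% and 130 for 57.5% v 42.5%. So 125 is plausible for base rates near 50%.

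**2. Does 258 follow?**
- Product of rates: 0.85 × 0.70 × 0.90 × 0.75 = 0.4016
- Retained from 258: 258 × 0.4016 = 103.6, about 104
- Contacts for 125: 125 / 0.4016 = 311.2, so 312
- Yield implied by the printed figures: 125 / 258 = 48.4%, against 40.2% from the rates

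The printed figure is not reproduced. It appears exactly if each loss is added on instead of divided out, with rounding at each step: 125 × 1.25 → 156; × 1.10 → 172; × 1.30 → 224; × 1.15 → 258. This is a likely origin, but the article does not state it.

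**3. What if some contacts are ineligible?** Contacts needed = 125 / (0.4016 × w). Retained from 258 = 258 × 0.4016 × w.

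| w (assumed) | contacts for 125 | retained from 258 | retained from 312 |
|---|---|---|---|
| 1.0 | 312 | 104 | 125 |
| 0.9 | 346 | 93 | 113 |
| 0.8 | 390 | 83 | 100 |
| 0.7 | 445 | 73 | 88 |
| 0.6 | 519 | 62 | 75 |

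**4. Power for a 15-point difference.** Power = Φ[(0.15 − 1.96·se0)/se1], where se0 is the pooled and se1 the unpooled standard error. Case rate first; base rates assumed.

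| cases v comparators | 50% v 35% | 57.5% v 42.5% | 35% v 20% |
|---|---|---|---|
| 125 v 250 | 0.80 | 0.79 | 0.88 |
| 104 v 208 | 0.72 | 0.71 | 0.81 |
| 104 v 520 | 0.82 | 0.80 | 0.89 |
| 83 v 166 | 0.62 | 0.61 | 0.72 |
| 83 v 520 | 0.74 | 0.73 | 0.84 |

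The row for 104 v 208 holds if 2:1 applies to analysed cases. The row for 104 v 520 holds if all 520 comparators are analysed whatever the number of retained cases.

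**5. Supply.** 522 × 21/12 = 913 eligible workers in the window. At the four stated rates, 913 × 0.4016 = about 367 could be retained.

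**The case against.** **The 258 may already count workers.** Sample size opens with a pool restricted to working persons, and the Abstract describes the 260 cases as employed. On this reading eligibility is applied upstream and 312 contacts give 125. The text allows this, so an extra shortfall beyond the multiplication error is conditional. The reading does not rescue 258 itself.

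**The registry may hold employment status.** A reader might infer that the registry cannot identify workers before contact. That is a reasonable inference from the order of steps in Recruitment, the clinical items listed, and the need to estimate the 522 from labour figures. The article does not say so. The list of registry items is introduced as non-exhaustive, and screening is described only for non-responders. A condensed article may leave screening logistics to the full protocol.

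**Contact with patients may be counted after doctor consent.** Dropping the 85% gives 0.70 × 0.90 × 0.75 = 0.4725, hence 258 × 0.4725 = 122 retained and 265 contacts for 125. That is close. But the sentence names doctor consent among the allowances that lead to 258, so this reading contradicts the text as written.

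**The study need not close short.** A reader might infer that it will. The article does not support this: nothing caps recruitment at 258, cases are defined by a diagnosis window, all patients with doctor consent are invited, and the pool is ample.

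**The power loss is not fixed by the text.** This stands. The base rates are assumed. At 35% v 20%, 104 cases at 2:1 still give 81%, and analysing all 520 comparators keeps 104 cases at about 80% or more in the scenarios shown.

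**Conclusion.** The contact figure is wrong on the article's own rates: 258 contacts retain at most about 104 cases, 21 below the 125 that the power statement uses, and 125 needs about 312. This requires no assumption beyond applying all four stated rates.

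The chain also carries no loss for ineligibility, and the article leaves open whether 258 and 260 are registry patients or eligible workers. If they are registry patients, the contacts needed rise to 125/(0.4016 × w). The size of that extra loss cannot be determined, because w is not given; 390 at w = 0.8 and 519 at w = 0.6 are illustrations. If they are eligible workers, w = 1 and only the multiplication needs correcting.

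Power at 104 cases and 2:1 is about 71-72% for base rates near 50%, against about 79-80% at 125. It is higher for base rates further from 50%, or if all 520 comparators are used. The defect lies in a planning number and its label; infeasibility is not shown.

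**What to change.** In Sample size:

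1. State whether 258 (and the 260 in the Abstract) counts registry patients contacted or eligible workers.
2. Restate the contacts as 125/(0.4016 × w). Take w from the labour figure already used for the 522, with an allowance for the listed exclusions. If eligible workers are meant, w = 1 and the number is 312.
3. Alternatively keep 258, state the expected analysed number (at most about 104), and give its power with the base rates assumed. For example, this is about 72% for 50% v 35% at 2:1.
4. Reconcile the 260 cases, 520 comparators and total of 780 with the chosen meaning, and say whether 2:1 applies to contacted, enrolled or analysed cases.

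The cost is a few revised sentences and, if 125 is kept, more letters to doctors and patients. About 913 eligible workers are expected over the 21 months, so supply does not stand in the way.

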**Methods/Design:**

An observational population-based study has been designed involving 260 adults newly-diagnosed with colorectal cancer between January 2010 and September 2011 and who were in paid employment at the time they were diagnosed. These cancer cases will be compared to a nationally representative comparison group of 520 adults with no history of cancer from the general population. Eligible cases will have a histologically confirmed diagnosis of colorectal cancer and will be identified through the Queensland Cancer Registry. Data on the comparison group will be drawn from the Household, Income and Labour Dynamics in Australia (HILDA) Survey. Data collection for the cancer group will occur at 6 and 12 months after diagnosis, with work questions also asked about the time of diagnosis, while retrospective data on the comparison group will be come from HILDA Waves 2009 and 2010. Using validated instruments administered via telephone and postal surveys, data will be collected on socio-demographic factors, work status and circumstances, and health-related quality of life (HRQoL) for both groups while the cases will have additional data collected on cancer treatment and symptoms, work productivity and cancer-related HRQoL. Primary outcomes include change in work participation at 12 months, time to work re-entry, work limitations and change in HRQoL status.

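### At the plan's own consent and retention rates, 258 initial contacts retain about 104 cancer patients at 12 months, not 125, and the contact count is then presented as the study size

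*Protocol article*

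**What the plan says.** The Sample size section bases the study on detecting a 15% difference in work participation, with a 5% significance level and 80% power. For the cancer group it lists the losses allowed for, "85% doctors consent, 70% participant consent, 90% baseline interview completions and 75% retention at 12 months post-diagnosis", and concludes that "we will require initial contact with 258 patients with colorectal cancer to retain 125 patients at 12 months".

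Comparators from the HILDA survey are to be matched two to each cancer patient. The section ends: "Thus the total sample size to be selected for the study will be approximately 780".

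The Methods/Design paragraph of the abstract describes the study this way: "An observational population-based study has been designed involving 260 adults newly-diagnosed with colorectal cancer". It sets these cases against 520 comparison adults.

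**The concern.** The four rates are successive steps, so the retained number is the contact number multiplied by all four. That calculation does not lead from 258 to 125. The ratio 125/258 is 48.4%, while the stated rates give 40.2%.

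The 125 retained cases are the target to which the 80% power statement is tied, and change in work participation at 12 months is a primary outcome. If recruitment is planned around 258, the analysed cancer group will be smaller than intended.

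The second problem is one of labelling. The 260 in the abstract is 258 rounded, and 780 is 260 + 520. A count of people to be approached therefore appears as the number of cancer patients in the study. A reader of the abstract would expect a cohort far larger than the one that will be interviewed or followed to 12 months.

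**Working it through.** **Inputs (all from the Sample size section).** Doctor consent 0.85; patient consent 0.70; baseline interview completion 0.90; retention at 12 months 0.75; initial contacts 258; target retained 125.

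**Forward from 258.**

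| Stage | Calculation | Patients |
|---|---|---|
| Contacted | – | 258 |
| Doctor consents | 258 × 0.85 | 219.3 |
| Patient consents | 219.3 × 0.70 | 153.5 |
| Baseline interview | 153.5 × 0.90 | 138.2 |
| Retained at 12 months | 138.2 × 0.75 | 103.6 |

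Starting from 260 instead gives 260 × 0.4016 = 104.4. The shortfall against 125 is 21, and 21/125 = 17%.

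**Backward from 125.** 125 / 0.401625 = 311.2, so 312 contacts are needed. That is 312 − 258 = 54 more than stated.

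**How 258 may have arisen.** If each stage is inflated by (1 + loss) instead of divided by the yield, rounding each time, the chain is 125 × 1.25 = 156, × 1.10 = 172, × 1.30 = 224, × 1.15 = 258. This gives the printed figure exactly and uses all four rates. It is an inference, because the article does not show its working.

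**Power.** The article gives no comparison-group proportion, so a range is assumed. The method is a two-proportion z test with pooled variance under the null, two-sided 5% (sidedness is not stated):

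power = Φ[(0.15 − 1.96 × SE0) / SE1]

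Here SE0 uses the pooled proportion and SE1 the separate ones. Example at 35% v 50% with 125 cases and 250 comparators: the pooled proportion is 0.40, SE0 = 0.0537 and SE1 = 0.0539. The power is Φ[(0.15 − 0.1052)/0.0539] = Φ(0.83) = 0.797.

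| Comparison v cancer proportion | 125 / 250 | 104 / 208 | 104 / 520 |
|---|---|---|---|
| 20% v 35% | 0.875 | 0.812 | 0.893 |
| 25% v 40% | 0.841 | 0.771 | 0.861 |
| 35% v 50% | 0.797 | 0.721 | 0.816 |
| 42.5% v 57.5% | 0.785 | 0.708 | 0.803 |

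The first column is close to or above 80% throughout, which fits 125 cases matched 2:1 as the basis of the stated power.

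**Size of the labelling problem.** 260/138 = 1.9 against those expected to be interviewed; 260/125 = 2.1 against the article's own retained figure; 260/104 = 2.5 against the retained number its rates imply.

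**The case against.** **Contact might be counted after doctor consent.** The Recruitment section has the doctor approached first and the patient written to only afterwards. If contact with the patient starts at that letter, three rates apply: 258 × 0.70 × 0.90 × 0.75 = 121.9, within 3% of 125. This is the best defence, but the Sample size section lists the 85% among the allowances that lead to 258. The reading also still falls short, since 125/0.4725 = 264.6, or 265 patients. And it would need about 258/0.85 = 304 names from the registry, a figure given nowhere. The text needs correcting on either reading.

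**Loss of power is not established.** This largely stands. The comparators are existing survey records, with 2,590 employed people of the right age available, and the abstract plans 520. If all 520 are analysed against 104 cases, power is about 80% or more across the table. The Background also offers an anchor: in an earlier Australian colorectal cohort, 33% of 621 men and 40% of 354 women were not working at 12 months. Pooled, that is (204.9 + 141.6)/975 = 35.5%. A 15-point difference puts comparators near 20.5%, where 104/208 still gives 0.807. However, the first hypothesis also counts changes in hours of 20% or more, which could raise the proportions. Nor do extra comparators help the analyses run in cancer patients only: the Cox models for return to work and the mixed models for quality of life and work limitations.

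**The shortfall need not occur.** Recruitment is not expressly capped at 258, and the registry is expected to supply enough patients. That makes the error easy to repair, but the stated target is still wrong.

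**The total of 780 is described as a number to be selected.** This softens that sentence, which sits beside the 125. The abstract has no such qualifier.

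**Conclusion.** The concern holds. On the four rates as stated, 258 contacts yield about 138 interviewed and 104 retained cancer patients. The target of 125 needs 312 contacts. This follows from the article's own figures and assumes only that the rates apply in sequence to the 258.

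The effect on power is conditional. At 2:1 matching to analysed cases, 104 cases give 71–77% if the comparison proportion is 25–42%, against 79–84% with 125. At a proportion of 20%, or with all 520 comparators analysed, 80% is essentially kept. The 17% loss falls in full on the analyses confined to cancer patients.

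The abstract's 260 and the total of 780 present a rounded contact count as the study size. The recruitment figure is wrong as written and must be corrected, because the sample size justification relies on it.

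**What to change.** In the Sample size section, do one of the following:

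- State 312 initial contacts to retain 125 at 12 months.
- Keep 258, state that about 138 are expected to be interviewed and 104 retained, and recalculate power with the number of comparators that will actually be analysed, naming the comparison-group proportion assumed.

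If contact was meant to start after doctor consent, say so, remove the 85% from the allowances behind the figure, state 265 patients contacted, and give the number of registry names needed (265/0.85 = 312).

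In the abstract, and where the total of about 780 is given, report the contacted, interviewed and retained numbers separately. State whether the 2:1 matching is to patients contacted (520 comparators) or to patients analysed (250 for 125 cases, 208 for 104).

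Cost: restating the yield is a text correction plus a power calculation. Raising the target to 312 means 54 more approaches, about 29 more baseline interviews (54 × 0.5355) and about 22 more patients followed to 12 months (54 × 0.4016), with their postal surveys. The article expects at least 522 eligible patients a year, or about 522 × 21/12 = 914 over January 2010 to September 2011, so the pool is sufficient.
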